#### Sensitivity and per-protocol analysis

Sensitivity analysis will be conducted by including only participants who completed the 24th voice message follow-up. A per-protocol analysis will be done to assess the effect of the intervention among the participants who have full follow-up with maternal health care service use. The participants who come for all ANC visits (first to fourth ANC visits) within the recommended time frame for ANC visits, and give birth at a health facility, will be considered as good protocol adherents for the primary outcome. The participants who do not come for ANC visits on the recommend time frame, mainly after the recommended time frame for ANC visits, and/or give birth out of a health facility, will be considered as poor adherents. Those participants who never come for ANC visits and give birth out of a health facility will be considered as non-adherents and not included in the sensitivity analysis.

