#### Control arm B

Participants in the control group will receive existing SOC which informs them about the advantages of maternal health care service use at HCs, informing them about the service which is given free of charge and giving appointments for regular follow-up. Unlike the intervention group, however, these participants will not be sent the voice message to remind for appointment and information about the advantage of maternal service use. With regards to the data collections, a house-to-house survey will be made among the households which will be identified with pregnant mothers who fulfill the inclusion and enrollment criteria. The three phases of the survey (I, II and III) will be made to collect data from the mothers who are in the trial. The survey will focus on maternal socio-demographic status, maternal health conditions, nutritional status, and health care service use and pregnancy outcome. The data collection tools will be the same for both trial arms (Trial arms A and B), except for mobile-phone-based voice message status.

For either intervention or control group if the study participants move from the study area before the study is completed, or withdraw from the study before the final data collection period, they will be registered as dropouts to follow-up.

Assuming that all mothers may give birth at different GAs their status of delivery will be tracked by fieldworkers and health professionals at selected HCs (Fig. 2).

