#### Primary outcome measures

This study has two primary outcomes (proportion of ANC use and institutional delivery). The assessment of outcome measures will be conducted starting from phase II data collection time (after the eighth voice message or 4 months from the date of enrollment) and at phase III data collection time (after the 24th voice message or at close-out time off study). All the participants in the trials will be interviewed about their ANC visits and place of delivery by using a structured questionnaire. Antenatal care service use is defined as maternal health care service use during pregnancy. The participants will be considered as an ANC service user if they have at least one ANC visit. Institutional delivery is giving birth at a health facility (Fig. 3).

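### Adherence is graded by ANC attendance and place of birth, not by receipt of messages, and women who fail both primary outcomes are dropped from the sensitivity analysis

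*Protocol article*

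**What the plan says.** The protocol article, under *Primary outcome measures*, sets two primary outcomes: ANC use and institutional delivery. For the first, "The participants will be considered as an ANC service user if they have at least one ANC visit"; the second is birth at a health facility. The *Analysis plan* analyses the primary outcomes by intention to treat and counts women lost to follow-up as non-users.

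The section *Sensitivity and per-protocol analysis* then gives these rules:

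- Sensitivity set: "Sensitivity analysis will be conducted by including only participants who completed the 24th voice message follow-up".
- Per-protocol set: the effect is assessed "among the participants who have full follow-up with maternal health care service use".
- Good adherents: women who attend the first to fourth ANC visits in the recommended windows "and give birth at a health facility, will be considered as good protocol adherents for the primary outcome".
- Poor adherents: women whose ANC visits fall outside the windows "and/or give birth out of a health facility, will be considered as poor adherents".
- Non-adherents, a rule that applies to the sensitivity set: "Those participants who never come for ANC visits and give birth out of a health facility will be considered as non-adherents and not included".

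Under *Control arm B*, "these participants will not be sent the voice message to remind for appointment".

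**The concern.** A per-protocol analysis asks what happened among women who received the treatment as planned. Here the treatment is a series of voice messages. The three adherence grades do not refer to the messages at all; they refer to ANC attendance and place of birth, which are what the messages are meant to change. Selecting women on those variables means selecting on the outcome after allocation.

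The exclusion of non-adherents has the same fault. The women removed are exactly those who fail both primary outcomes, and more of them are expected in the arm with lower uptake.

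At stake is the use of the supporting analyses. Counting every loss as a non-user is a strong assumption, and a reader will look to the sensitivity analysis to test it. If observed non-users are removed as well, a difference from the primary result cannot be put down to the handling of missing data.

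**Working it through.** **Inputs from the protocol.** Institutional delivery is 47% in control and 60% in intervention (*Sample size determination*, which treats health-professional-assisted delivery as institutional delivery). The planned difference is 60 − 47 = 13 points, as the protocol states, and RR = 0.60/0.47 = 1.277. These are the rates behind the sample size: the continuity-corrected two-proportion formula (two-sided 5%, 80% power) gives 246 per arm, and 246 × 1.3 = 319.8, that is, the stated 320.

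**Inputs not in the protocol.** It gives no ANC rate by arm and no association between ANC use and place of birth. Both are assumed below and varied.

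**Step 1. Good adherents only.** Four timely visits imply at least one visit, so ANC use = 1. A facility birth means institutional delivery = 1. Both proportions are 100% in each arm, so RR = 1.00 and the difference is 0, whatever the true effect.

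**Step 2. Dropping double failures, independence assumed.** Let d be the share dropped in an arm: d = (1 − delivery rate) × (1 − ANC rate). Retained delivery rate = delivery rate/(1 − d). So retained RR = true RR × (1 − d_control)/(1 − d_intervention).

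| Assumed ANC use, control v intervention | d control | d intervention | Retained delivery rates | RR (true 1.28) |
|---|---|---|---|---|
| 34% v 50% | 0.53 × 0.66 = 0.350 | 0.40 × 0.50 = 0.200 | 72.3% v 75.0% | 1.04 |
| 60% v 75% | 0.53 × 0.40 = 0.212 | 0.40 × 0.25 = 0.100 | 59.6% v 66.7% | 1.12 |
| 80% v 90% | 0.53 × 0.20 = 0.106 | 0.40 × 0.10 = 0.040 | 52.6% v 62.5% | 1.19 |

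In the middle row, about 68 of 320 control women (320 × 0.212) and 32 of 320 intervention women (320 × 0.100) are removed. The ANC outcome is distorted too: 0.60/0.788 = 76.1% v 0.75/0.900 = 83.3%, so its RR falls from 1.25 to 1.09.

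**Step 3. Independence relaxed.** Let f be the share of non-facility births with no ANC visit. Retained delivery rate = p/(p + (1 − p)(1 − f)).

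- Same f in both arms: RR = 1.24 at f = 0.2 and 1.08 at f = 0.8.
- Messages halve f: RR = 1.19 (0.2 v 0.1), 1.09 (0.4 v 0.2), 0.99 (0.6 v 0.3) and 0.875 (0.8 v 0.4).
- No true effect on delivery (47% in both arms), f = 0.4 v 0.2: control 0.47/0.788 = 59.6%, intervention 0.47/0.894 = 52.6%, a spurious RR of 0.88.

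**Step 4. The message criterion.** Read literally, completing the 24th message can be met only in the intervention arm, because control women are sent none. The total of 24 also includes a maximum of 21 messages up to week 42 (*Trial arm A*), so a woman who enrols later or delivers earlier has fewer due.

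**The case against.** Four objections deserve weight.

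1. A reader might infer that the per-protocol RR is bound to be 1.00. The protocol does not support that as a certainty. It never says that the per-protocol set is good adherents only, and its description of that set could mean complete follow-up of service use or full use of services. Poor adherents might be kept, or the grades merely tabulated. This stands, and the 1.00 is conditional. The grades remain outcome-based on either reading.

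2. The section does contain an exposure criterion, the 24th message, so it would be too strong to say that the sensitivity analysis ignores the intervention. This stands. The criterion is then combined with an outcome-based exclusion and has no literal counterpart among controls. Because Phase III follows the 24th message, the phrase might be meant as completing close-out, which could apply to both arms; if so, the text should say that.

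3. A reader might infer that the bias always pulls the RR towards 1 and stops there. Step 3 shows that it need not: the RR can pass below 1, or depart from 1 when there is no effect on delivery.

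4. The primary analysis is by intention to treat, and no decision rule is attached to these analyses. This stands and limits the severity. It does not make the rules sound.

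Good adherence is also stricter than the ANC outcome (four timely visits against one). It implies success on both outcomes without being the same variable, and that implication is all the argument needs.

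**Conclusion.** The point holds for the supporting analyses. Adherence is defined by service use that determines the primary outcomes, and women who fail both are removed from the sensitivity analysis. This is a stated rule that biases the contrast, not a detail left to another document.

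The 1.00 result applies only if the per-protocol set is good adherents alone. The range of 1.04 to 1.19 against a planned 1.28 rests on the assumed ANC rates and on independence within arm. Independence is doubtful, since both are care-seeking by the same woman, and other dependence assumptions give values from 1.24 down to 0.875. The existence of the bias is secure; its size is not known.

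A reader might infer that the trial's main result is compromised. The protocol does not support this: the intention-to-treat analysis, its risk ratio and the sample size are untouched. Should-fix.

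**What to change.** - Delete the good, poor and non-adherent grades as criteria for any analysis set. Exclude no woman from any analysis because of her ANC use or place of birth.
- Run the sensitivity analysis on women with completed Phase III follow-up, applied alike in both arms, and present it as a check on counting losses as non-users.
- Define the per-protocol set by eligibility and, in the intervention arm, by a pre-stated share of the messages due for each woman's own enrolment and delivery dates. Use the message status already planned for Phases II and III.
- Label the per-protocol result as non-randomised supporting evidence, because exposure is selected in one arm only.

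The cost is mainly wording, and *Trial status* says that participant selection has not started. Two limits remain. Phone confirmation of messages is stated only for Phase II, and no sending log is described, so the source of the message count needs to be named. The per-protocol result also stays open to selection by engagement, since women who receive most of their messages may differ from those who do not.

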#### Sub-group analysis

Exploratory sub-group analysis will be done to identify whether the effects of intervention vary with socio-demographic characteristics, maternal health condition, nutritional status and previous health care service use difference among the participants. If statistically significant heterogeneity is identified, then relative risk with 99% confidence intervals will be estimated.

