### Sample size determination

A study which was conducted in Zanzibar showed that 60% of the intervention group used a health-professional-assisted delivery (institutional delivery), as compared to 47% in the control group; based on this evidence, sample size required for this study is calculated as follows [16]:P_1_ = proportion of health professional assisted delivery in control group = 47%P_2_ = proportion of health professional assisted delivery in intervention group = 60%

Based on the above information, a sample size required for this study is calculated by using STATA/SE software with consideration of sample size for a two-sample comparison of proportions [17].

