### Assumption and hypothesis for sample size calculation

*H*_o_: *P*_1_ = *P*_2_, whereas *P*_1_ is the proportion in the intervention group (population _1_) and *P*_2_ is the proportion in the control group (population _2_), *α* is level of significance at 95% confidence interval, and *β* is power.

In a cluster-RCT the study subjects within the cluster are more likely to interact, respond in the same manner and can no longer act independently which can lead to a loss of statistical power. This intracluster dependence can be quantified by considering intracluster correction coefficient (ICC) and design effects (DE) [18]. Hence, the estimated sample size per group is inflated by considering ICC, and DE of 1.3. Thus, the final sample size required for this study will be 320 for each control and treatment groups.

*Description of sample size calculation*: a sample size of 640 pregnant mothers (320 in each of the treatment and control group) will be sufficient to detect a clinically important difference of 13% between groups in the m-health intervention, using a two-sided test of 80% power (*β*) and 5% of significance level (*α*) with 95% confidence interval**.** The 13% difference represents the difference between a 60% health-professional-assisted delivery rate in the intervention group as compared to the control group [16].

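### Sub-group relative risks are planned only after a significant heterogeneity test, so the estimates printed are selected for lying far apart and their 99% intervals can fall short of 99% coverage

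*Protocol article*

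**What the plan says.** The Sub-group analysis section of the protocol plans exploratory analyses of whether the effect varies with "socio-demographic characteristics, maternal health condition, nutritional status and previous health care service use difference among the participants". It then states the reporting rule: "If statistically significant heterogeneity is identified, then relative risk with 99% confidence intervals will be estimated". It gives no level for the heterogeneity test, no number or size of sub-groups, and no adjustment for the selection. No other section provides for sub-group RRs when the test is not significant.

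The only significance level in the protocol is in the sample-size section ("5% of significance level", two-sided). Under Statistical method, the RRs for the primary and secondary outcomes carry 95% intervals and do not depend on any preliminary test.

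**The concern.** A 99% interval covers the truth 99% of the time over all the occasions on which it could be computed. If it is shown only after a significant heterogeneity test, the occasions that reach the reader are those in which the sub-group estimates lie far apart. When there is little or no true heterogeneity, the distance is mostly chance: the larger RR is too high, the smaller is too low, and each interval is centred too far from the truth. The wider interval presumably serves as caution for sub-group results, and the condition removes part of that caution.

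At stake is how sub-group results are read. A reader would see a selected set of contrasts with intervals that look more dependable than they are. For the other factors, the protocol plans no RR that could serve as a comparison.

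**Working it through.** **Inputs.** Event proportions 47% control and 60% intervention (Sample size determination). 320 women per arm, two-sided 5%, 80% power, design effect 1.3 (Assumption and hypothesis for sample size calculation). Interval level 99%, critical value 2.576 (Sub-group analysis). Assumed because not stated: heterogeneity test at 5% (range 1% to 10%), two equal sub-groups of 160 per arm, independent women.

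**The plan's own figure.** n = [1.96·√(2·0.535·0.465) + 0.8416·√(0.47·0.53 + 0.60·0.40)]² / 0.13² = (1.3825 + 0.5886)² / 0.0169 ≈ 229.9, so 230. With continuity correction: (230/4)·[1 + √(1 + 4/(230·0.13))]² ≈ 245.1, so 246. Then 246 × 1.3 = 319.8, so 320 per arm. The stated size reproduces, and I use it below.

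**Coverage, no true heterogeneity.** Let a and c be the errors of the two sub-group log RRs in standard-error units, independent N(0,1). The heterogeneity statistic is D = (a − c)/√2, and the pair is printed if |D| > 1.96. Given D = d, a is normal with mean d/√2 and variance 1/2. Even a pair that only just passes (d = 1.96, mean 1.386, SD 0.707) has coverage Φ[(2.576 − 1.386)/0.707] = Φ(1.68) ≈ 0.954, and coverage falls as |d| grows. Integrating over |D| > 1.96:

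| Heterogeneity test level | Coverage of each printed 99% interval, equal sub-groups |
|---|---|
| 1% | 76.6% |
| 5% | 89.1% |
| 10% | 92.9% |

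At 5%, both intervals cover together about 78% of the time. With 3, 4 or 5 equal sub-groups, per-interval coverage is 88.7%, 89.3% and 90.1%. With a 30/70 split it is 84.5% in the smaller sub-group and 93.4% in the larger.

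**Binomial check.** Simulated RRs at 47% v 60%, 160 per arm per sub-group: 89.6-89.9% per interval given printing, against 99.1% for the same intervals always reported. The loss comes from the selection, not from the interval method. With the sample reduced by the design effect of 1.3, coverage is 90.1%.

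**Exaggeration, no true heterogeneity.** The variance of each sub-group log RR is (0.40/0.60 + 0.53/0.47)/160 = 0.01121, so the SE of the difference is √(2 × 0.01121) = 0.150. A pair must differ by about 1.96 × 0.150 = 0.294 to be printed, a ratio of RRs of at least about e^0.294 = 1.34. The median of |D| given |D| > 1.96 is the point with upper tail 0.025/2 on each side, 2.241, so the median ratio (larger over smaller) is e^(2.241 × 0.150) ≈ 1.40; simulation agrees. The truth is 1.00. A larger-over-smaller ratio exceeds 1 even without the condition, but its median is then only e^(0.6745 × 0.150) ≈ 1.11. In the simulation the true common RR is 0.60/0.47 = 1.28, while the printed pair has median larger RR 1.53 and median smaller RR 1.08.

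**Modest real difference.** Intervention-arm rates 65% and 55%, control 47% in both: the true ratio is 65/55 = 1.18. Simulated coverage is 98.2% and 97.4%. The median printed ratio is 1.44. The SE of the difference is again about 0.150, so the minimum printable ratio of about 1.34 already exceeds 1.18.

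**Larger real difference.** Coverage is 97.0% when the interaction test has 17% power and 99.0-99.4% when it has 50-90% power.

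**The case against.** The strongest case on the other side has five parts.

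- **The shortfall is conditional.** It needs both a significant test and little true heterogeneity, and coverage is close to nominal once a real difference exists. This stands, and it limits the size of the point. The exaggerated ratio under a modest real difference remains.
- **The rule does not print more wrong intervals in absolute terms.** With no heterogeneity, the chance that a given interval is printed and misses is 0.05 × (1 − 0.891) ≈ 0.5%, against 1% if it is always printed. This is correct and is the trade-off of the fix. But a reader judges the intervals that are on the page, and for those the stated 99% does not hold.
- **The test level is not stated.** This also stands, so 89-90% must be given with its range of about 77% to 93%. A reader might infer that the stricter 1% level was put on the interval and withheld from the test. The protocol does not say what level the test uses, so that is not established.
- **The section does not say that other results will be withheld.** A reader might infer that factors without heterogeneity are barred from the report. The text supports less: it makes the RRs with 99% intervals conditional and provides for nothing else. The layout of the sub-group table may be left to a fuller document, but the condition itself is stated here.
- **Clustering.** The randomization section describes one purposively chosen health centre per arm, so every sub-group RR also carries any difference between districts. Unconditional intervals would not reliably reach 99% either. This is a separate matter that the present fix does not solve.

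**Conclusion.** The point holds as a minor improvement to an exploratory analysis. The condition selects sub-group estimates for being far apart. With a 5% test, two equal sub-groups, no true heterogeneity and no clustering modelled, each printed 99% interval covers about 89-90% of the time, and the median ratio of RRs is about 1.40 against a true 1.00. The coverage figure moves between about 77% and 93% as the assumed test level moves from 1% to 10%, and smaller sub-groups do worse than larger ones. Under a modest real difference coverage is 97-98%, with the ratio about 1.44 against 1.18.

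Two stronger readings are not supported. The 99% intervals are not unreliable in general: reported unconditionally they cover 99.1% in the same simulation, and under clear heterogeneity they are near nominal even with the condition. Nor does the point touch the main results: the intervals for the primary and secondary outcomes do not depend on a preliminary test. The exploratory label lowers the weight of sub-group conclusions, but it does not restore the coverage printed beside them.

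**What to change.** Delete the opening condition of the sentence. State instead that, for every listed baseline sub-group factor, the RR with its 99% interval in each level and the interaction p-value will be reported whatever the heterogeneity test shows, and that all of these will be interpreted as exploratory.

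Do not add a rule that highlights factors with an interaction p-value below 0.01. Sub-groups highlighted that way are selected again. With no true heterogeneity and equal sub-groups, their 99% intervals would cover only about 77% of the time.

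The cost is one sentence and a larger table or forest plot, with more intervals on show. Data collection, sample size and the primary analysis do not change.

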### Statistical method

For primary and secondary outcomes, Relative Risk with 95% confidence interval will be estimated. The association of dependent and independent variables will be checked by using the chi-square test. For count data, further analysis will be done by using multivariate count data logistic regressions or the Poisson Regression Model will be used to examine the effect of treatment on trial arms and Kaplan-Meier survival analysis will be used to compare maternal health care service use over time among treatment and control groups. Moreover, to adjust for both the clustering effect of the districts with their respective HCs and the participant-level intracluster correction, Generalized Estimating Equation (GEE) models will be used. All the analysis will be done by using STATA software.

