**Methods/design:**

Through, a cluster-randomized controlled trial, 640 participants will be selected based on their districts and respective health centers as the unit of randomization. All pregnant mothers who fulfill the inclusion criteria will be allocated to a mobile-phone-based intervention and existing standard of care or control with a 1:1 allocation ratio. The intervention consists of a series of 24 voice messages which will be sent every 2 weeks from the date of enrollment until the close-out time. The control group will receive existing standard of care without voice messages. Data related to outcome variables will be assessed at three phases of the data collection periods. The primary outcome measures will be the proportion of antenatal care visits and institutional delivery, whereas the secondary outcome measures will consist of the proportion of postnatal care visits and pregnancy outcomes. Risk ratios will be used to a measure the effect of intervention on the outcomes which will be estimated with 95% confidence interval and all the analyses will be done with consideration of clustering effect.

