### Analysis plan: analysis of primary and secondary outcome

In this study, data will be collected at three phases. Phase I data collection will be done during enrollment time; phase II data collection will be conducted after 4 months of enrollment or after the eighth voice message; and end-line data collection or close-out time data collection (phase III data collection time) will be made after the 24th voice message. All the data will be checked for completeness at the time of data collection, coded and entered into Epi-Info-7 by using double-data entry method and they will be transported to STATA software Version 11 for analysis. Data cleaning will be done by the running of simple frequency distributions for internal consistency.

The report of this findings will be made according to the Consolidated Standards of Reporting Trials (CONSORT) standards for reporting RCTs. This is a behavioral intervention which is unlikely to cause adverse effects. Hence, the analysis will be done after the close-out time of the data collection. Intention-to-treat (ITT) principles will be used for primary outcome analysis; therefore, all the participants will be analyzed according to the arms they will be randomized to. During ITT analysis, the participants lost to follow-up, resulting in missing to maternal health care service use at close-out time of data collection, will be considered as non-health care service users.

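### An ordinary chi-square test stands beside GEE with neither named as deciding for the primary outcomes, and the chi-square contradicts the protocol's own commitment to allow for clustering

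*Protocol article*

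**What the plan says.** The Statistical method section fixes the effect measure for primary and secondary outcomes as a relative risk with 95% confidence interval. It then says "The association of dependent and independent variables will be checked by using the chi-square test". Count or Poisson regression follows, restricted to count data. Next, "Kaplan-Meier survival analysis will be used to compare maternal health care service use over time among treatment and control groups". Last, GEE is added to adjust for clustering by district and health centre. No sentence says which of these supplies the deciding relative risk or p-value for a primary outcome.

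On clustering, the abstract (Methods/design) states that "all the analyses will be done with consideration of clustering effect". The section on assumptions for the sample size inflates the per-group number by a design effect of 1.3 and arrives at 320 per arm.

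On timing, Primary outcome measures says "The assessment of outcome measures will be conducted starting from phase II data collection time" and continues to Phase III. It defines both primary outcomes as binary: at least one ANC visit, and birth at a health facility. The Analysis plan section says "the analysis will be done after the close-out time of the data collection". It prescribes intention-to-treat for the primary outcomes, and counts as non-users those lost to follow-up, "resulting in missing to maternal health care service use at close-out time of data collection".

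On allocation, Randomization and sampling procedure assigns two districts by lottery, one to each arm, and takes one purposively chosen health centre in each.

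**The concern.** A chi-square test on individual women treats all 640 as independent. The abstract rules that out for every analysis, and the sample size calculation assumes it is untrue. The two statements cannot both be followed, so an analysis plan that filled in detail would still have to override one of them.

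While the conflict stands, two analyses of the same primary outcome are on the table, and they can give opposite answers near the 5% boundary. A reader of the results could not tell which one had been chosen in advance. The unclustered test is always the more favourable of the two when the design effect exceeds 1, so the ambiguity runs in one direction.

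For ANC there is a second, smaller gap. Any visit by Phase II and any visit by close-out are different contrasts, both are collected, and neither is labelled as the deciding one.

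**Working it through.** **Inputs.** Control 47%, intervention 60% (Sample size determination). Two-sided 5% level, 80% power, design effect 1.3, 320 per arm (Assumption and hypothesis for sample size calculation).

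**1. Reproduce the stated sample size.** The uncorrected number per arm for two proportions is

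n = [1.96·√(2·0.535·0.465) + 0.8416·√(0.47·0.53 + 0.60·0.40)]² / 0.13² = 229.9.

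With the continuity correction,

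n′ = (n/4)·[1 + √(1 + 4/(n·0.13))]² = 245.04, rounded up to 246.

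Then 246 × 1.3 = 319.8, so 320 per arm. The stated figure reproduces. It belongs to one two-sided 5% comparison of proportions with the variance inflated by 1.3.

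**2. True error of the unclustered test.** If the real variance is DE times the one the chi-square assumes, the rejection probability under no effect is 2·[1 − Φ(1.96/√DE)].

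| Design effect | True two-sided error |
|---|---|
| 1.1 (assumed, for range) | 6.2% |
| 1.3 (protocol) | 8.6% |
| 1.5 (assumed, for range) | 11.0% |

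At the protocol's own value the error is 8.6/5 = 1.7 times the stated level.

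**3. Range of opposite verdicts for institutional delivery.** At a pooled proportion of 0.535 (midpoint of 47% and 60%),

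SE = √(2·0.535·0.465/320) = 0.0394.

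- Chi-square is significant from 1.96 × 0.0394 = 7.7 points.
- With the variance multiplied by 1.3, significance starts at 1.96 × √1.3 × 0.0394 = 8.8 points.

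Fixing control at 47% and letting the pooled value move with the difference gives nearly the same limits, about 7.8 and 8.8 points.

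**4. Worked example inside that range.** Take 178/320 against 150/320, a difference of 8.75 points and a relative risk of 1.19.

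- Chi-square: z = 0.0875/0.0395 = 2.21, p = 0.027.
- With design effect 1.3: z = 2.21/√1.3 = 1.94, p = 0.052.
- 95% interval for the relative risk, from SE(log RR) = √[(1 − 0.556)/178 + (1 − 0.469)/150] = 0.0777: 1.02 to 1.38 unadjusted. With 0.0777 × √1.3 = 0.0886, it is 0.998 to 1.41.

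**5. Timing.** Enrolment is below 16 weeks' gestation and Phase II is 4 months later, so Phase II falls at roughly 33 weeks at the latest. Institutional delivery is therefore in effect known only at Phase III, and the timing question concerns ANC alone.

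**The case against.** Four points on the other side deserve weight.

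- **Much is already fixed.** The relative risk with 95% interval, intention-to-treat, binary definitions, analysis after close-out and the close-out rule for missing data are all stated. Together they point to a clustering-adjusted close-out relative risk. This stands, and it narrows the gap. It does not remove the chi-square, nor does it label the adjusted result as deciding.
- **The chi-square may be only a first bivariate check.** It concerns dependent and independent variables generally, and the independent variables include covariates. That reading is possible. But the voice message heads the same list of independent variables, so the sentence also covers the treatment comparison, and the abstract's commitment has no exception for preliminary tests.
- **Model detail belongs in an analysis plan.** True for the specification of the GEE model. A conflict between two printed statements is not missing detail.
- **The design cannot estimate the adjustment.** With one district and one health centre per arm, variation between those units is inseparable from the treatment effect. This is correct. The figures above hold for an imposed design effect of 1.3, not one estimated from the trial, and the remedy has to say so.

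A reader might infer something stronger: that both primary outcomes pass through four methods at two survey times, with a correspondingly large multiplicity problem. The text does not support that. Count models are limited to count data, whereas both primary outcomes are binary. Kaplan-Meier is for use over time. Delivery has no real Phase II comparison. Any overall error rate across visit counts and visit times would need attendance patterns that the protocol does not give.

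**Conclusion.** The point holds in a limited form. An unclustered chi-square is listed beside GEE with no statement of which decides, and it contradicts both the abstract and the design effect behind the sample size. Taking the protocol's 1.3 at face value and a normal approximation, the chi-square's true error is about 8.6% instead of 5%. The two approaches disagree for delivery differences of about 7.7 to 8.8 points, a band roughly 1 point wide and below the planned 13. A result outside that band gives the same verdict at the 5% level either way. The choice between Phase II and Phase III is open for ANC only, and the analysis plan already leans to close-out.

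This is worth correcting before results are seen, but it does not by itself show that the trial will reach a wrong conclusion.

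**What to change.** In Statistical method:

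1. Remove the ordinary chi-square as a test of the primary outcomes.
2. Name as deciding, for each binary outcome defined in Primary outcome measures, the Phase III (close-out) intention-to-treat relative risk with 95% interval, allowing for clustering.
3. Label Phase II comparisons, visit counts and Kaplan-Meier curves as supportive.
4. State that GEE cannot estimate clustering at district or health-centre level, because each arm has only one of each. Then either base the interval on a lower-level cluster such as the kebele, or inflate the variance by the protocol's own 1.3. State that neither option removes the confounding of district with treatment.

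The cost is a few sentences. The target of 320 per arm is unchanged, and the article reports that participant selection has not started. With the 1.3 imposed, the interval is √1.3 = 1.14 times as wide, about 14% more, on the log scale. The kebele option could give a different width, which the protocol's figures do not determine. An unclustered or Phase II result could no longer be claimed as the primary finding.
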